### Outcomes {12}

The primary outcome is change in Insomnia Severity Index (ISI) score, measured as change from baseline to day 14.

Secondary outcomes include change in alcohol craving score from baseline to days 7 and 14, percent of total days abstinent during the 14-day practice quit attempt, mean number of drinks per drinking day as measured by the Timeline Follow Back, and change in PTSD symptoms as measured by change from baseline to days 7 and 14 in the CAPS-5 and PCL-5 score(s).

Exploratory outcomes include actigraphy sleep metrics for sleep latency onset (SLO), wake after sleep onset (WASO), and total sleep duration, as well as the change in PROMIS Sleep Disturbance *T*-score from baseline to day 14.

### Participant timeline {13}

The overall study design is outlined in Fig. 1. Assessments administered at each visit are detailed in Table 1.

**Table 1 Tab1:**
[figure not shown]
Procedures and measures administered at each study visit

*PLC* Placebo

* = Randomization will follow EtG confirmation of alcohol abstinence between Day –1 and Day 0

** = Urine Pregnancy Test is only required for female participants

P Primary Endpoint

S Secondary Endpoint

E Exploratory Endpoint

C Includes Alcohol Urge Questionnaire (AUQ), Profile of Mood States (POMS), and Visual Analog Scale (VAS)

Green Columns = The screening process may take up to two in-person days to complete

Blue Columns = Participants are to complete visit in person

#### Pre-screening, consent, and screening

Potential participants will initially be pre-screened by a trained research staff via phone. Participants meeting basic eligibility criteria will then be scheduled for a screening visit with a study staff member. The screening visit will take place in a private office where the research procedures, risks, and benefits associated with the study will be reviewed. Once a participant has signed the consent form, they will complete eligibility assessments across 1 or 2 days (days −7 and −6) that will be reviewed by trained research staff and the principal investigator (PI) to determine study eligibility.

#### Open label placebo lead-in

If determined eligible for the study, all participants will be given placebo for days −7 to −1 leading up to randomization (day 0) and reinformed that they are receiving placebo for this portion of the study. To ensure compliance with study drug self-administration, participants will be required to complete medication check-ins daily via CAROMA check-ins for the entire duration of their participation in the study.

On day −2, participants will be asked not to drink for the next 2 days, which will be confirmed by the EtG test on day 0. If the EtG test is positive, thus failing the participant, participants will be given an additional attempt to not drink for 2 days. If the EtG test is again positive, the participant will be screened out of the study. If the EtG test is negative during the first or second attempt, the participant will proceed to the rest of the baseline (day 0) assessments and randomization.

#### Baseline

On day 0, participants will be required to complete the visit in person. Participants will be considered enrolled in the study once they have provided consent, deemed to meet eligibility criteria, successfully completed the placebo lead-in period, and received confirmation of alcohol abstinence via the EtG test results. Participants will be randomized to suvorexant or matched placebo using a computer-generated algorithm coded in the electronic data capture (EDC) system with appropriate notifications to masked and unmasked study staff. Randomizations will be stratified on sex and level of sleep disturbance (ISI score) via the algorithm provided by PASA Data Coordinating Center (DCC).

At the conclusion of the visit, participants will be given an actigraph wearable device to capture daily sleep information. They are instructed to wear the device starting on day 0 through day 14. Participants will be administered either 10 mg SUV or matching placebo based on a masked randomization allocation for days 0 to 6.

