### Objectives {7}

The primary objective of this study is to assess the initial efficacy of SUV (20 mg) in improving sleep metrics.

The secondary objectives of this study are:To assess the effect of SUV (20 mg) on cue-induced alcohol craving.To evaluate the effect of SUV (20 mg) on the mean number of drinks per drinking day.To evaluate the effect of SUV (20 mg) on drinks per day during the medication period over a 14-day quit attempt.To assess the initial efficacy of SUV (20 mg) in reducing PTSD symptoms.

The exploratory objectives of this study are:To assess the efficacy of SUV (20 mg) in improving sleep latency onset (SLO), wake after sleep onset (WASO), and total sleep duration via actigraph data.To evaluate the effect of SUV (20 mg) on National Institutes of Health Patient-Reported Outcomes Measurement Information System (PROMIS) sleep scale scores.

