### Intervention description {11a}

The study will utilize 10 mg and 20 mg SUV tablets and matching placebo obtained from Merck & Co., Inc., Rahway, NJ, USA. One SUV tablet (10 mg/20 mg) or placebo tablet will be taken orally once daily 30 min before bed with at least 7 h remaining prior to planned awakening. Each participant will be given a placebo run-in (day −7 to day −1). On day −2, participants will be prompted to initiate a 48-h abstinence period. If the study team determines appropriate quit attempts were successful on (verified by self-report + BrAC + EtG) baseline (day 0), the participant will be randomized to SUV or placebo and administered 10 mg SUV or placebo capsules for an additional 7 days (day 0 to day 6). On day 7, the participant previously randomized to SUV will be given 20 mg SUV, and the participant previously randomized to placebo will continue with placebo. The participant will be administered the remaining number of capsules (days 7–13).

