#### Medical procedures and/or assessments

Breathalyzer: Breathalyzer tests are used to measure participants’ breath alcohol concentration (BrAC). Samples >0.01 g/dl are considered positive. Results are kept in research records and not entered in medical records.Ethylglucuronide (EtG) testing: Ethylglucuronide is a byproduct of ethanol (alcohol that one drinks) and glucuronide, a common biological compound made in the liver that binds various toxins and drugs in the body that allows them to be excreted in the urine. When someone drinks even relatively small amounts of alcohol, EtG is formed and can be detected in the urine.Demographics: The interviewer asks the respondent for his/her date of birth, race, if he or she considers himself or herself to be Hispanic or Latino, and highest-grade level or degree received at the time of the interview.Medical history: This measure is a broad screening tool to collect information on a participants’ medical history, including recent hospitalizations, and check for conditions such as diabetes, liver disease, and kidney disease. It is comprised questions to cover the following areas: allergies, asthma, head, ears, eyes, nose, throat (HEENT), cardiovascular, renal, hepatic, pulmonary, gastrointestinal, musculoskeletal, neurologic, psychiatric, dermatologic, metabolic, hematologic, endocrine, genitourinary, reproductive system, seizure, infectious disease, inflammatory or auto-immune disorders, and diabetes. Screening will include questions to ensure patients are not currently taking any CPY3a inhibitors.Physical examination (PE): A targeted PE will include assessments of the head, eyes, ears, nose, throat, skin, thyroid, neurological system, lungs, cardiovascular system, abdomen (liver and spleen), lymph nodes, and extremities. Height and weight measurements will be taken during screening.Electrocardiogram (ECG): 12-lead ECGs will be obtained using a machine that automatically calculates heart rate and determines intervals for PR, QRS, QT/QTc, and PRT axes.Colombia Suicide Severity Rating Scale (C-SSRS): is a short questionnaire that screens for individuals at risk for suicide.Adverse events: All AEs occurring during the clinical trial will be collected, documented, and reported by the principal investigator/designated study staff according to the specific procedures detailed in section 22 below. Additionally, study staff will assess patients for any medical or psychiatric side effects by asking the participant “How have you been feeling since I saw you last?” and in a manner consistent with Systematic Assessment for Treatment of Emergent Events (SAFTEE) guidelines [25]. Study staff will also review the previous Adverse Event Form and inquire whether any of those events are continuing. Each new or unresolved adverse event will be recorded on the Adverse Event Case Report Form using a brief verbatim term, a severity ranking, and any additional description, according to the procedures. If an adverse event is reported that requires medical attention, it will be reported to a study clinician immediately for review. The PI/trained staff member will review each AE to assess their possible relationship to study medications and expectedness.Prior/concomitant medications (con-meds): Concomitant medications (con-meds) are other prescription medications, over the counter (OTC) drugs, or dietary supplements that a study participant takes in addition to the drug under investigation. Participants are asked to bring all their current medications with them at the time of their screening appointment.Actigraph: This wearable device will be used to measure the SLO and WASO variables in detecting activity and sleep patterns of participants. Participants will be given this device upon successful screening into the study.

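### Handing out the actigraph at the end of day 0 leaves the placebo lead-in unrecorded, and another section points to an earlier hand-out; the two need reconciling

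*Protocol article*

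**What the plan says.** The protocol article gives two times for issuing the actigraph.

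- The Baseline section, describing the in-person day 0 visit, says: "At the conclusion of the visit, participants will be given an actigraph wearable device to capture daily sleep information". It continues: "They are instructed to wear the device starting on day 0 through day 14".
- The actigraph entry under Medical procedures and/or assessments says: "Participants will be given this device upon successful screening into the study".

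The section on pre-screening, consent and screening puts the eligibility assessments on days −7 and −6. Placebo is then taken openly from day −7 to day −1. Randomized medication starts on day 0 (Baseline: "Participants will be administered either 10 mg SUV or matching placebo based on a masked randomization allocation for days 0 to 6"), and according to Intervention description {11a} the tablet "will be taken orally once daily 30 min before bed".

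Objectives {7} lists as an exploratory aim the efficacy of suvorexant in "improving sleep latency onset (SLO), wake after sleep onset (WASO), and total sleep duration via actigraph data". Outcomes {12} lists the same metrics without defining them as change from baseline; in that sentence only the PROMIS score is a change score. Statistical methods {20a} makes every comparison beyond the primary and the five secondary measures descriptive.

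**The concern.** If the Baseline section governs, every actigraphy night falls after randomization and after the evening dose. The lead-in is the only stretch in which objective sleep could be recorded before randomized drug, and it would go unrecorded. The first treatment week cannot stand in for a baseline, because the active arm is already on suvorexant.

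The abstract and the background present objective and subjective sleep measures together as the means of assessing a putative mechanism, and the Discussion names actigraphy as an innovative feature for elucidating mechanisms. The ISI, craving, PTSD and PROMIS outcomes are all expressed as change from baseline. Objective sleep alone could not be.

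The two hand-out times also matter for conduct. With two sites, one could follow the Baseline section and the other the procedures list, so that lead-in nights exist at one site and not at the other. No later analysis can recover nights that were not recorded.

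**Working it through.** The article gives no figure for actigraphy, so there is none to reproduce. The check has two parts.

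**1. Nights recorded before randomized drug**

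| Hand-out | Wear | Nights before randomized dosing |
|---|---|---|
| End of day 0 (Baseline) | Days 0 to 14 | 0, since the day 0 dose is taken before that night's sleep |
| Day −7 (procedures list, screening done in one day) | Day −7 onward, if worn from hand-out | 7 (days −7 to −1) |
| Day −6 (procedures list, screening done over two days) | Day −6 onward, if worn from hand-out | 6 (days −6 to −1) |

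Participants are prompted on day −2 to stop drinking for 48 hours. The nights of days −2 and −1 therefore fall in prompted abstinence, leaving 7 − 2 = 5 or 6 − 2 = 4 earlier nights. A participant who needs a second abstinence attempt would have a different pattern.

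*Which day does successful screening mean?* Eligibility criteria {10} ties screening to day −7/−6. The notes to Table 1 allow screening up to two in-person days. Sample size {14} lists screening, placebo lead-in and day 0 activities as separate stages. These favour day −7/−6. Against them, the lead-in section says of the abstinence check at day 0: "If the EtG test is again positive, the participant will be screened out of the study". That usage lets screening run to day 0.

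**2. Precision that a baseline would add**

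Let ρ be the correlation between a participant's lead-in mean and treatment-period mean. The article does not give ρ, so a range is assumed. Against an unadjusted comparison of treatment-period means, adjustment for the lead-in mean multiplies the standard error by √(1 − ρ²). The equivalent sample size ratio is 1/(1 − ρ²).

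For scale, take the article's 76 participants less its 7% attrition: 76 × 0.93 = 70.7, so 70 analysable, 35 per arm. A two-sided t-test at 0.05 with 80% power then detects 0.68 SD without a baseline. With one, this becomes 0.68 × √(1 − ρ²). This only illustrates precision, as no test of actigraphy is planned.

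| Assumed ρ | √(1 − ρ²) | Cut in SE | 1/(1 − ρ²) | Detectable difference (SD) |
|---|---|---|---|---|
| 0.3 | √0.91 = 0.95 | about 5% | 1.10 | 0.65 |
| 0.5 | √0.75 = 0.87 | 13% | 1.33 | 0.59 |
| 0.7 | √0.51 = 0.71 | 29% | 1.96 | 0.49 |

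These gains are upper figures for a model that also holds site, sex and baseline ISI. To the extent that those covariates already explain variation in objective sleep, the extra gain from the lead-in mean is smaller.

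**The case against.** A reader might infer that, without a baseline, improvement in objective sleep cannot be measured at all. The article does not support that. Allocation is 1:1 and randomized against placebo, so the between-arm difference in on-treatment values estimates the drug's effect without bias, and the exploratory aim can be read as that contrast. Outcomes {12} does not define the actigraphy metrics as change scores, so no stated endpoint becomes uncomputable. Nor does the article plan an analysis relating actigraphy change to change in ISI, craving or PTSD symptoms. All of this stands.

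A reader might also take the conflict over hand-out time as certain. It is likely, but the procedures entry names no day, participants count as enrolled only after the lead-in and the abstinence check, and the body of Table 1 is not available here. If the procedures entry does govern and means day −7/−6, lead-in data may exist and the loss does not arise. This too stands, and is itself a reason to state one time.

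The outcome is exploratory and descriptive, subjective sleep has a baseline through ISI and PROMIS, and the precision gain depends on an assumed correlation. These limit the importance of the point. They do not remove it: precision still sets the width of a descriptive estimate, and unrecorded nights stay unrecorded.

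**Conclusion.** The point holds as a cheap improvement and a needed reconciliation. It does not invalidate any planned analysis. Under the Baseline section there are no actigraphy nights before randomized drug; under the most natural reading of the procedures list there could be six or seven. The first schedule keeps an unbiased randomized comparison but gives up within-person change, a check of balance in objective sleep, change-on-change mechanism analysis and baseline-adjusted precision. The precision loss lies between slight (about 5% of the standard error at ρ = 0.3) and appreciable (29% at ρ = 0.7). It rests wholly on the assumed ρ and is measured against an unadjusted analysis. The absence of baseline nights rests on the Baseline section being the instruction that sites follow.

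**What to change.** State one hand-out time in both sections and in the visit schedule. Preferably issue the device at eligibility confirmation (day −7/−6), with wear through day 14. Analyse treatment-period means adjusted for the lead-in mean plus site, sex and baseline ISI. Prespecify whether the nights of prompted 48-hour abstinence count toward the baseline, since they may differ from earlier lead-in nights, and how a second abstinence attempt is handled.

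The cost is about one more week of wear per participant with the same devices, plus retrieving devices from participants who fail the abstinence check.

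If day 0 hand-out is kept, correct the procedures entry and reword the exploratory aim in Objectives {7} as a between-arm difference during treatment. That costs only the edit, but the lead-in nights are then forgone.

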#### Virtual follow-up

For days 1 to 6, participants will complete daily visits over the phone and complete online questionnaires on their past-days’ drinking, alcohol craving, mood, sleep, and PTSD symptoms via the EDC. Safety outcomes will also be collected through daily self-report. CAROMA check-ins will be completed daily at the time of medication self-administration.

#### In-person follow-up

On study day 7, participants will be scheduled for an in-person visit. At the conclusion of the visit, participants will be administered either 20 mg of SUV or matching placebo based on masked randomization allocation from baseline (day 0).

#### Virtual follow-up

For days 8 to 13, participants will continue the real-world practice quit attempt, during which they will attempt to stop drinking for the remaining 6 consecutive days. Participants will complete daily visits over the phone and complete online questionnaires on their past-days’ drinking, alcohol craving, mood, sleep, and PTSD symptoms via the EDC. Safety outcomes will also be collected through daily self-report. CAROMA check-ins will be completed daily at the time of medication self-administration.

#### Final study visit

On the final study day (day 14), participants will complete the last round of study assessments in person. Participants will return unused medication during this visit and cease CAROMA check-ins.

### Sample size {14}

Sample size for this study was determined based on the prior published studies of suvorexant effect on ISI which suggest that the standard deviation (SD) is between 6 and 8 points for the change from baseline. Based on a two-sided *t*-test of treatment effect with 80% power and alpha set at 0.05, the study would be able to detect a medium effect size (about 0.66, e.g., mean difference of 5.5 with SD of 7) with a total of 76 participants. This total number of participants includes those that complete screening, placebo lead-in, and at least day 0 study activities through randomization (and assuming no more than 7% attrition/loss to follow-up).

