While this trial is fully powered to detect a significant effect for the primary aim (sleep as measured by the ISI), one limitation to be noted is that the other outcome measures (alcohol use over 14 days; cue-induced alcohol craving, PTSD symptoms) should be considered effect-size generating rather than confirmatory, and thus provisional in the context of the study. A second limitation is the 14-day trial duration. This duration was selected specifically to test a Go-signal for initial efficacy during a 14-day quit attempt period, similar to approaches used in previous AUD pharmacotherapy studies (e.g. [32],). This 14-day trial period can clearly only provide a provisional test of SUV on the selected outcomes. A third limitation is that the study funding period and protocol do not allow for the collection of follow-up data, e.g., 3- and 6-month outcomes. These above-noted limitations will necessitate larger multisite RCTs with more standard durations (i.e., 12–16 weeks) and appropriate long-term follow-up observations to advance SUV toward regulatory approval for the treatment of AUD and PTSD.

The successful completion of the current study will advance SUV, a promising novel compound with existing preclinical, safety, and efficacy data in SUD [18, 33] and PTSD [34]. A determination of statistically significant results for the primary and/or secondary aims is expected to provide justification for a larger, longer-duration confirmatory multisite trial in the treatment of co-occurring AUD and PTSD.

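### The sample-size example does not match its own effect size: 5.5 ISI points with an SD of 7 is 0.79, not about 0.66

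*Protocol article*

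**What the plan says.** The Sample size section {14} of the protocol article takes from earlier suvorexant studies that the "standard deviation (SD) is between 6 and 8 points for the change from baseline". It plans a two-sided t-test with "80% power and alpha set at 0.05" and concludes that the study can "detect a medium effect size (about 0.66, e.g., mean difference of 5.5 with SD of 7) with a total of 76 participants". The 76 are counted through randomization, "assuming no more than 7% attrition/loss to follow-up".

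Three other sections bear on the point. Sequence generation {16a} sets 1:1 allocation. The section on missing data {20c} rules out imputation. Statistical methods {20a} makes the day-14 change in ISI the single primary hypothesis, analysed by a linear model with treatment, site, sex and baseline ISI.

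**The concern.** The bracket prints a standardized effect, a raw difference and an SD, and offers the last two as an example of the first. Any two of them fix the third, and here they disagree. The word *about* cannot absorb the gap, since 0.79 is 19% larger than 0.66. All the figures are printed in the article, so this is neither an extraction fault nor a detail left to the SAP.

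The section is the only justification that the article gives for 76 participants, and it concerns the one primary test. A reader who takes the standardized effect at SD 7 believes the design difference is 4.6 ISI points. A reader who takes the example believes it is 5.5. Someone reusing the example for a later trial would credit 76 participants with 80% power for a difference at which the power is in fact 90% or more.

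**Working it through.** **Inputs.** From Sample size {14}: two-sided t-test, alpha 0.05, power 80%, effect about 0.66, example of 5.5 points with SD 7, SD range 6 to 8, 76 randomized, attrition at most 7%. From Sequence generation {16a}: 1:1 allocation, so 38 per arm.

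**Step 1. Analysed number after attrition.** 7% of 76 is 5.3, so at most 5 can be lost within the cap (5/76 = 6.6%; losing 6 would be 7.9%). That leaves 71, taken here as 36 and 35. With no imputation, those lost drop out of the day-14 comparison.

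**Step 2. Does the plan's own figure reproduce?** Power is computed from the noncentral t distribution with noncentrality λ = d × √(n₁n₂/(n₁+n₂)) and n₁+n₂−2 degrees of freedom.

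- 76 analysed: λ = 0.66 × √19 = 2.877, critical t (74 df) = 1.993, power 81.0%.
- 71 analysed: λ = 0.66 × √17.746 = 2.780, critical t (69 df) = 1.995, power 78.3% (79.4% by the normal approximation).

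Both lie within two percentage points of 80%. So 0.66 goes with 76 participants, at least approximately.

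**Step 3. Does the example give 0.66?** With d = difference / SD:

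| Difference | SD | d |
|---|---|---|
| 5.5 | 6 | 0.917 |
| 5.5 | 7 | 0.786 |
| 5.5 | 8 | 0.688 |

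None is 0.66. Solving backwards, 5.5 / 0.66 = 8.33, an SD outside the stated range, and 0.66 × 7 = 4.62 points.

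**Step 4. Power and sample size for the example as printed (d = 0.786).**

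- 76 analysed: λ = 3.425, power 92.2%.
- 71 analysed: λ = 3.310, power 90.4%.
- Needed for 80% power: 27 per arm, 54 in total; 54 / 0.93 = 58.1, so 59 randomized.

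The example therefore leads neither to 80% power nor to 76 participants.

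**Step 5. Effect detectable with 80% power.**

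| Analysed | d | Points at SD 6 | SD 7 | SD 8 |
|---|---|---|---|---|
| 76 | 0.651 | 3.9 | 4.6 | 5.2 |
| 71 | 0.674 | 4.0 | 4.7 | 5.4 |

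**Step 6. A possible source of the mismatch.** With 5.5 points and SD 8 (d = 0.688), 80% power needs 35 per arm, 70 in total, and 70 / 0.93 = 75.3, which rounds up to 76. This reproduces the planned number exactly. It is only an inference: the article states SD 7 and 0.66, and 0.69 is not 0.66 either.

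**The case against.** The best defence is that the slip does no harm. For 5.5 points, the only raw difference that the article names, power with 71 analysed is 96.8% at SD 6, 90.4% at SD 7 and 81.5% at SD 8. It stays above 80% over the whole stated SD range after the full permitted attrition. The number randomized, the alpha, the test and the analysis all stay as they are. A null result can also be judged from the 95% confidence interval that Statistical methods {20a} promises. All of this stands, and it limits the point to a correction of the text.

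It also disposes of two stronger readings. A reader might infer that the Discussion is wrong to say "While this trial is fully powered to detect a significant effect for the primary aim (sleep as measured by the ISI". The figures do not show that, because the 5.5-point difference keeps at least 81% power.

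A reader might also infer that attrition breaks the claim for 0.66. After the maximum stated loss, power for exactly 0.66 is 78.3% and the detectable effect is 0.674 (0.665 by the normal approximation), which is close to what the article calls about 0.66. The planned model also adjusts for baseline ISI, site and sex, whereas the calculation uses an unadjusted t-test. If those covariates explained about 4% of the variance of the change, the detectable effect with 71 would return to 0.66, since 0.674 × √0.96 = 0.66. That 4% is an assumption, as the article gives no figure. The attrition point is a remark, not an error.

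Calling 0.66 a medium effect is a matter of label. The number stands beside it, so nobody is misled about its size.

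What the defence does not remove is the contradiction itself. No other section of the article corrects it, and harmlessness does not make 5.5/7 equal 0.66.

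**Conclusion.** Wrong as written. The difference, the SD and the standardized effect in the sample-size sentence are mutually inconsistent: the example gives 0.79 where the text says about 0.66. At SD 7 the gap is 5.5 − 4.6 = 0.9 ISI points, and the power attached to the example is understated by 10 to 12 percentage points (90% with 71 analysed, 92% with 76, against the stated 80%).

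The article does not show which of the three numbers is the misprint, so the target difference is unclear rather than known to be one value or the other. Nor does it support saying that the trial is underpowered.

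The ratio needs no assumption. The power figures rest on the article's own t-test, equal allocation and 71 evaluable under the 7% cap.

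**What to change.** The sponsor should say which inputs produced 76 and restate the sentence with one consistent set of difference, SD, standardized effect and evaluable number. If the number randomized and the attrition cap are kept, wording such as this would be consistent:

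> With 76 randomized and no more than 7% attrition (71 evaluable), the study has 80% power (two-sided alpha 0.05, t-test) to detect a difference of about 0.67 SD, that is 4.7 ISI points at an SD of 7 (4.0 to 5.4 points for SDs of 6 to 8).

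The example of 5.5 points with SD 7 should be corrected, removed, or given with its own power of about 90%.

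The cost is a change of wording, with no additional participants and no change to the analysis. It is best made before unblinding, so that the benchmark for the primary result is fixed in advance.
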